**Primary outcome:**

Changes in muscle strength of extensors of the knee, walking speed, number of repetitions in the sit-leave test, and change in the lean mass in kilograms.

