
**Summary:**

The high prevalence of sarcopenia in the elderly and the role of exercise training in reversing it is well-known. However, there are several limitations that prevent the elderly from adhering to a regular physical training program to increase the muscle strength or mass and to reduce the risk of falls. Recently, whole-body electrostimulation has been reported to be effective for recovery from sarcopenia, with a short period of intervention. This study aims to evaluate the effectiveness of whole-body electrostimulation in improving the function, and muscle strength and mass in the elderly, as well as in reducing their fear of falling and increasing social participation, compared to conventional resistance training. The subjects will be elderly people, with no cognitive and neurological impairment, and no acute or chronic diseases or musculoskeletal ailments that prevent them from performing resistance exercise. The sample will be randomized to two groups. The electro-stimulation group will undergo 18 minutes of electrical stimulation of the muscles, two sessions a week, for eight weeks. The regimen will be an intermittent bipolar electric current with a frequency of 85 Hz, pulse width of 350 μs, with 6 seconds of stimulation and 4 seconds of rest. The resistance training group will perform exercises with a load of 50 to 80% of 1-RM in supervised sessions, twice a week, over a period of 8 weeks. Muscle strength will be evaluated by Microfet manual dynamometer; functional evaluation will be determined by gait speed, TUG test, and sit-up test; muscle mass will be evaluated by electrical bioimpedance, questionnaires will be used to evaluate the fear of falling and degree of social participation. The intergroup data will be compared by paired t-test or Mann-Whitney test according to the tested normality. Longitudinal evaluations after 3 and 6 months of training will be conducted through questionnaires, to evaluate the degree of social participation and the fear of falling. The effect size will be determined for each variable of interest. Analysis of mixed models, including the outcomes measured at the 4 time points (basal, after intervention, 3 and 6 months) will be performed. It is expected that the results of this study will determine the effectiveness of whole-body electrostimulation in improving the functional capacity of the elderly and in reducing the risk of falls.

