**Primary objective**

The primary objective of this study is to compare the effect of whole-body electrostimulation and conventional resistance training on functional capacity, muscle strength, walking speed, risk of falling, and lean mass among elderly subjects.

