**Evaluation of strength of extensors of the knee:** Strength of the quadriceps muscles will be evaluated during the left and right knee extension, using the Microfet manual dynamometer (DMM) by means of isometric tests (Annex VI). The DMM is a reliable and valid assessment tool for measuring the muscle strength during knee extension in the elderly (Arnold 2010). With the participant sitting on a high chair, with the feet not touching the ground, the legs in a vertical position, and the dynamometer applied perpendicular to the leg proximal to the malleolus (Figure 1) and fixed by a strap to the chair, and the determination of the angulation of knee flexion will be performed with goniometer. The participant must push to extend the knee against the manual dynamometer. During the evaluation the verbal command will be given as "*stretch the knee by using greater force, stretch, stretch"*. This measure will be performed five times, and the highest and lowest force values recorded will be discarded. The average of the three remaining values will be calculated, and the isometric strength of the knee extensor muscles will be recorded in Newtons.

[figure not shown]

Figure 1. Patient positioning for evaluation of the extension force of the knee.

**Evaluation of muscle mass:** The body composition will be measured using the electrical bioimpedance apparatus *Biodynamics* tetrapolar, commonly described in the literature, which is a digital instrument, providing the values of resistance and reactance. The examination is performed by passing a low electric current (500 to 800 μA and 50 kHz) through the participant’s body, this imperceptible to the participant (Annex VII).

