**Fear of falling** will be assessed by the International Falls-Efficacy Scale-Brazil (FES-I-BRAZIL) (Annex IX). The FES-I-Brazil is an adapted and validated scale for the Brazilian population that has adequate intra and inter-evaluator reliability. This questionnaire will be administered by the researcher physiotherapist trained for this evaluation, and will be conducted through an interview in a private and reserved environment. It comprises questions about 16 varied daily activities, from simple activities such as bathing, to activities that require a greater degree of independence, such as participation in social activities (Camargos et al, 2007). Each item has a score ranging from 1 to 4 points. A score of ≥ 23 is considered to be associated with sporadic fall history and ≥ 31 points is associated with recurrent fall.

**Intervention:** After the baseline evaluation and randomization, the participants will be submitted to one of the two muscle training modalities (electro-stimulation or resistance) for a period of eight weeks, as described below. For each training modality (electro-stimulation or resistance) a maximum of two participants will be allowed to undergo simultaneous training. Regardless of the training modality, two slots per week will be offered to each participant: Tuesdays and Thursdays or Mondays and Wednesdays during the morning or afternoon periods.

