**Data analysis methodology:**

**Statistical analysis**

SPSS version 20.0 will be used. The data will be presented as average and SD or median and interquartile. Statistical analysis by intention to treat will be performed using the unpaired t-test or Mann-Whitney test. The effect size will be determined for each variable of interest. Analysis of mixed models, including the outcomes measured at the 4 time points (basal, immediately after intervention, and at 3 and 6 months) will be performed. The "time point" will be included as a class variable. Group, time, and group * time interactions will be inserted. This will evaluate the sole effect of the intervention, since the difference from baseline values at each time point will be evaluated. A value of p = 0.05 will be assumed for all tests.

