**Secondary outcome:**

Changes in fear of falling assessed by FES-I/Brazil and social participation by Life-H.

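### Four unranked primary outcomes are each tested at 0.05 with no success rule, and risk of falling is in the primary objective without a primary outcome

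*Protocol*

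**What the plan says.** The Primary outcome section of the protocol names "Changes in muscle strength of extensors of the knee, walking speed, number of repetitions in the sit-leave test" and, as a fourth item, change in lean mass in kilograms. It gives no order and no rule for combining them.

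The Statistical analysis section plans between-group comparisons by unpaired t-test or Mann-Whitney test, together with mixed models. On the significance level it says "A value of p = 0.05 will be assumed for all tests". It mentions no adjustment and does not say whether one, some or all of the primary outcomes must reach significance.

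The Primary objective section compares the two trainings on "functional capacity, muscle strength, walking speed, risk of falling, and lean mass among elderly subjects". The Secondary outcome section lists "Changes in fear of falling assessed by FES-I/Brazil and social participation by Life-H". The Summary expects the results to determine effectiveness in "improving the functional capacity of the elderly and in reducing the risk of falls".

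Two measurement details matter. For knee extensors, "Strength of the quadriceps muscles will be evaluated during the left and right knee extension", and the three retained readings are averaged, but the text does not say how the two legs become one value. TUG is described under Functional physical evaluation and appears in Table 2 at baseline and post-intervention, yet it is in neither outcome list.

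**The concern.** With four outcomes of equal rank and no success rule, whichever reaches p < 0.05 can be presented as the primary result, in favour of either training. The nominal 5% then describes each test but not the primary claim as a whole. This is not a detail left open for a later analysis plan: the protocol itself sets 0.05 for all tests, so a plan that adjusted would depart from it.

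The second part is a mismatch between objective and outcomes. A conclusion on risk of falling is a primary aim, but no primary outcome carries it. An unlisted measure such as TUG could be brought forward or left out after the data are seen.

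**Working it through.** **Inputs from the protocol.** Four primary outcomes (Primary outcome); 0.05 per test (Statistical analysis); 33 per arm, 66 in total (Sample Size). Tests are taken as two-sided, which the protocol does not state. It gives no correlations between outcomes, so a range is assumed. It states no familywise error rate, so there is no figure of its own to reproduce.

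**Familywise error if one significant outcome is enough, with no true difference on any.**
- Independent outcomes: 1 − 0.95^4 = 1 − 0.8145 = 0.1855, or 18.5%.
- Upper bound under any dependence: 4 × 0.05 = 0.20, or 20%.
- Simulation of four t-tests with 33 per arm and equal correlation between all pairs (100,000 runs for each value):

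| Assumed correlation | At least one p < 0.05 | All four p < 0.05 |
|---|---|---|
| 0 | 18.4% | 0.0% |
| 0.3 | 17.4% | 0.02% |
| 0.5 | 15.7% | 0.15% |
| 0.7 | 13.2% | 0.56% |
| 0.9 | 9.5% | 1.8% |

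The last column shows how much depends on the missing rule: the same data and tests give very different error rates under one rule or the other.

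**With adjustment.** Holm on four tests compares the ordered p-values with 0.05/4 = 0.0125, 0.05/3 = 0.0167, 0.05/2 = 0.025 and 0.05. With no true differences, a false claim requires the smallest p-value to pass 0.0125. For independent outcomes that has probability 1 − 0.9875^4 = 4.9%, and it is at most 4 × 0.0125 = 5%.

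**Cost at the first Holm step, 33 per arm.**
- Difference detectable with 80% power (noncentral t): 0.70 SD at 0.05 and 0.84 SD at 0.0125.
- Power per outcome at an assumed 0.7 SD, normal approximation: 0.7 × √(33/2) = 2.843. Then Φ(2.843 − 1.960) = 81% at 0.05, and Φ(2.843 − 2.498) = 64% at 0.0125. The noncentral t gives slightly lower values, 80% and 61%.
- By the normal approximation, 80% power at 0.0125 for 0.7 SD would need 46 per arm.

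**Objective set against outcomes.**

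| Primary objective | Primary outcome |
|---|---|
| Functional capacity | Sit-to-stand repetitions |
| Muscle strength | Knee-extensor strength |
| Walking speed | Walking speed |
| Lean mass | Lean mass in kg |
| Risk of falling | None |

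Four of the five domains are matched. For the fifth, the nearest declared measure is the falls efficacy scale (FES-I). It is a secondary outcome and is named as fear of falling, which the protocol treats as a separate, secondary objective. TUG is measured but undeclared, and the protocol does not itself link it to risk of falling. No count of falls is described.

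**The case against.** **The 18.5% needs a rule that the protocol does not state.** This is correct, and the figure is conditional on it. But the protocol does not exclude the rule either, and that gap is the defect.

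**A reader might take 18.5% as a ceiling, or as the trial's actual error rate.** It is neither. It is the independence value. The bound is 20%, and outcomes that move together give less, down to 9.5% at a correlation of 0.9.

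**The hypothesis is equal effectiveness, so false claims of a difference look beside the point.** This stands in part. The figure does not measure the error of reading p > 0.05 as equal effect, which is a separate problem, and a stricter threshold would make such a reading easier. But the planned tests are tests of difference, and the Benefits section contemplates effectiveness of electrostimulation over resistance training being proven, so difference claims are in scope.

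**A reader might infer that requiring all four to succeed would rescue the claim of equal effectiveness without adjustment.** The protocol does not support this. It gives no margin, so success on that claim is undefined for every outcome.

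**A reader might infer that falls have no outcome of any kind.** That goes too far. FES-I is a declared secondary outcome, and the protocol says that a score of 23 or more "is considered to be associated with sporadic fall history and" one of 31 or more with recurrent falls. What is missing is a primary outcome for a primary aim.

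**A reader might count five tests by treating each leg separately, giving 1 − 0.95^5 = 22.6% if independent.** The protocol names strength as one outcome and nowhere says that the legs are tested apart. The text only leaves open how they are combined.

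**The Summary states an expectation, not a commitment.** This is fair. The expectation still has no declared primary outcome behind it.

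**Conclusion.** The point holds in this form. Four primary outcomes are unranked, each is tested at 0.05, and no rule says how many must succeed. If one significant outcome is enough for a claim of a difference, the familywise error is 18.5% under independence, 20% at most, and roughly 9.5% to 17% over assumed correlations of 0.9 down to 0.3. These figures assume two-sided tests and no true difference on any outcome, and the correlations are assumptions. They say nothing about the error of claiming equal effectiveness.

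The mismatch needs no such assumptions: one of the five domains in the primary objective has no primary outcome, and TUG is measured twice but declared nowhere. Both matters should be corrected, and neither requires a change to the design.

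**What to change.** 1. In Primary outcome and Statistical analysis, state that the four outcomes at the post-intervention visit form the primary family, and that any claim of a between-group difference uses Holm at an overall 0.05 (0.0125, 0.0167, 0.025, 0.05). Naming the visit matters because Procedures and Instruments also mentions an evaluation eight weeks after the intervention, which Table 2 does not show.
2. Add that a non-significant result is not evidence of equal effectiveness. Do not offer an all-four rule for that claim while no margin is defined.
3. Define one strength value per participant, for example the mean of both legs.
4. List TUG as a secondary outcome.
5. Either remove risk of falling from the Primary objective and the matching expectation from the Summary, or tie both explicitly to a declared outcome.

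These are wording changes with no new visits or measurements. The cost is sensitivity: at the first Holm step with 33 per arm, the difference detectable at 80% power rises from about 0.70 to 0.84 SD. At an assumed 0.7 SD, power per outcome falls from about 81% to 64%. Later Holm steps cost less.

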**Secondary outcome:**

Changes in fear of falling assessed by FES-I/Brazil and social participation by Life-H.

**Sample Size:**

It is expected that 66 elderly people will be involved in the study, 33 in each arm. However, to understand the size of the effect, a pilot study with 10 subjects will initially be conducted to confirm our forecast based on the sample calculation.

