**Will there be use of secondary data sources (medical records, radiographs, demographic data, etc.)?**

(X) Yes ( ) No

| **Inform the number of individuals approached personally, recruited, or who will undergo some form of intervention:**  **66** | | | **Number:**  **66** |
| --- | --- | --- | --- |
| **Groups into which research participants will be divided** | | | |
| **Group** | **No. of participants** | **Interventions to be carried out** | |
| Group  Electro-stimulation | 33 | Functional evaluation: walking speed, TUG test and sit-up test. Evaluation of the strength of extensor muscles of the knee. Evaluation of lean body mass. Degree of social participation and evaluation of fear of falling. Muscle training by electro-stimulation of the entire body. | |
| Group  Resisted Training | 33 | Functional evaluation: walking speed, TUG test, and sit-up test. Evaluation of the strength of extensor muscles of the knee. Evaluation of lean body mass. Degree of social participation and evaluation of fear of falling. Muscle training through resistance exercises. | |

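### A 10-subject pilot cannot confirm or refute the forecast of 66 by estimating the effect; limit it to feasibility and keep N fixed

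*Protocol*

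**What the plan says.** The Sample Size section of the protocol reads: "It is expected that 66 elderly people will be involved in the study, 33 in each arm". It then adds a pilot, run "to understand the size of the effect", and says that "a pilot study with 10 subjects will initially be conducted to confirm our forecast based on the sample calculation". The pilot's declared job is therefore to estimate the effect. Feasibility and the SD are not mentioned.

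The section does not give the pilot's split between arms, what result would count as confirmation, what would follow from any other result, or whether the ten are among the 66.

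The group table, under the question on secondary data sources, answers the item "Inform the number of individuals approached personally, recruited, or who will undergo some form of intervention" with 66, divided 33 and 33, and lists no pilot group. The Execution Schedule lists no pilot stage.

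Under Statistical analysis, the comparison is by "unpaired t-test or Mann-Whitney test", and "A value of p = 0.05 will be assumed for all tests". The Hypothesis section supposes that electrostimulation and resistance training are equally effective.

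**The concern.** A pilot meant to confirm a sample size through the observed effect is useful only if its estimate is precise enough to separate a correct forecast from a wrong one. With about five people per arm, the sampling error of a standardised difference is as large as the effect that 33 per arm is able to detect. Agreement with the forecast would then be largely luck, and so would disagreement.

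If the team acted on the result, it could shrink, enlarge or drop the trial because of noise. If the ten also stayed in the final analysis after N had been changed on the strength of their arm comparison, the final test would no longer hold its nominal 5% level.

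**Working it through.** **Inputs from the protocol.** 33 per arm and a pilot of 10 (Sample Size); significance level 0.05 and an unpaired two-group comparison (Statistical analysis).

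**Assumptions, because the protocol does not state them.** Two-sided testing, 80% power, normal data, and a pilot split 5 and 5, which is the most favourable split.

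**1. What 33 per arm detects.** The protocol shows no effect, SD or power, so 66 cannot be reproduced, only solved backwards.
- Normal approximation: d = √(2/33) × (1.960 + 0.842) = 0.246 × 2.802 = 0.69 SD.
- With the t distribution: 0.70 SD.
- At 90% power: 0.80 and 0.81 SD.

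**2. Precision of the pilot.**
- Even with a known SD, the standard error of the difference is √(2/5) = 0.63 SD.
- An observed d of 0.70 gives t = 0.70 × √(5/2) = 1.11 on 8 degrees of freedom. The noncentral-t 95% confidence interval for d is -0.60 to 1.96.
- The pilot has 16% power at d = 0.70. It would need a true effect of about 2.0 SD for 80% power.

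**3. What sample size the pilot would imply.** The usual formula is n per arm = 2(1.960 + 0.842)²/d² = 15.70/d². A size between half and double 33 per arm (17 to 66) therefore needs an observed d between √(15.70/66) = 0.49 and √(15.70/16) = 0.99. Simulated pilots of 5 + 5 with a true d of 0.70, the case in which 33 per arm is right, gave:

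| Result | Share or range |
|---|---|
| Central 95% of pilot estimates | -0.59 to 2.45 SD |
| Right sign and within 20% of 33 per arm | 8% |
| Right sign, between half and double 33 per arm | about 29% |
| Right sign, 16 per arm or fewer | about 35% |
| More than 66 per arm, or wrong sign | about 36% |
| Wrong sign alone | 13% |

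The implied n per arm has a median of 29 and an interquartile range of 11 to 114. The half-to-double share is 27% for a true d of 0.5 and 29% for 0.8, so the picture does not depend on the back-solved value.

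**4. If the arms are truly equal,** as the Hypothesis section supposes, the absolute pilot effect is still at least 0.69 SD in 31% of pilots.

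**5. Type I error, in a hypothetical use of the pilot.** Suppose that n per arm is reset to 15.70/d² within chosen bounds, that the ten are kept in the final analysis, and that the final test is a two-sided 5% t-test. Simulation under no difference gives:
- bounds 10 to 66 per arm: 7.0%
- bounds 33 to 66 per arm: 5.4%
- N fixed at 33 per arm: 5.0%

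**The case against.** The strongest reply is that the protocol contains no rule to misuse. It announces a pilot and an expected 66, and the group table records 66 as the number. Nothing says that N will move. This stands, and it rules out several stronger readings.

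- **A reader might infer that the plan will halve, double or abandon the trial on the pilot result.** The text sets no threshold and no consequence. Such harm is conditional on someone acting on the result.
- **A reader might infer that the pilot misleads more often than it supports 66.** That depends on what support means. If it means agreement within a factor of two, about 29% of pilots agree. If it means only that 33 per arm is enough, 52% of pilots say so at a true d of 0.70 and 58% at 0.80. Of those 52 points, 35 also say that about half the trial would do. The statement still cannot be made without a definition.
- **A reader might infer a type I error of 7%.** That needs pooling, an arm comparison at the pilot stage, a reset of N from the observed effect, and permission to shrink to 10 per arm. The protocol states none of these.
- **A reader might take the ten as an interim look inside the 66.** The group table points towards inclusion but does not settle it, and handling of pilot data may be covered in an analysis plan that is not at hand.

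It is also fair to say that 5 per arm, 80% power and 0.70 SD are assumptions. The imprecision does not hinge on them: results are similar for true effects from 0.5 to 0.8 SD, and an unequal split would be less precise.

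**Conclusion.** The concern holds in a limited form. A pilot of ten cannot do what the Sample Size section asks of it: its effect estimate is compatible with anything from a moderate effect in the wrong direction to a very large one in the right direction. Confidence in that is high.

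The sizes quoted rest on the assumed 5/5 split, two-sided 5% and 80% power. The consequence for N and for type I error is conditional, because no rule for changing N is stated; with N held at 33 per arm the error stays at 5%.

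The step also sits badly with the protocol's own hypothesis. For a claim of equal effectiveness, the sample size turns on a margin and an SD, and an observed between-arm effect is not the quantity that would confirm it. For the same reason, presenting 66 as enough to detect 0.70 SD would justify it for a superiority question that the Hypothesis section does not ask.

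**What to change.** In the Sample Size section:

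1. Limit the pilot to feasibility: recruitment, duration of the tests and completion. State that no between-arm effect from it will set, confirm or change N.
2. Keep 66 fixed on the basis of the existing sample calculation, expressed as a margin and an SD to match the Hypothesis section. For orientation, under a true difference of zero, one-sided 2.5% and 80% power, 33 per arm corresponds to a margin of √(2/33) × 2.802 = 0.69 SD. The authors would have to say whether a margin of that order is acceptable.
3. Say whether the ten count towards the 66. They may count if no arm comparison is made at the pilot stage. Otherwise exclude them from the analysis and reconcile the group table, since 66 + 10 = 76 people would then take part.

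If the team wants the pilot to inform the SD, it should do so cautiously. With 8 degrees of freedom the 95% interval runs from 0.68 to 1.92 times the estimate.

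The cost is a few sentences and no extra participants, provided the ten are counted within the 66. What is lost is an early look at the effect, which at this size carries almost no information.
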